### Cognitive function

3.7

For screening cognitive decline, MMSE is the most common used screening scale.^[24]^ It contains domains of orientation, memory, attention, language, and visuospatial ability.^[25]^ However, studies also showed that MMSE has deficiency on detecting mild cognitive impairment (MCI) and clinical signs of dementia.^[26,27]^ It is superior for more advanced stages, meanwhile MoCA is more useful for the mild stages of the cognitive impairment.^[28]^

Thus, we also use MoCA, which is a cognitive screening, diagnostic, and tracking tool with high sensitivity and specificity for detecting MCI,^[28]^ to evaluate the cognitive function. MoCA also has superiority on detecting executive dysfunction compared with the MMSE.^[29]^ It assesses several cognitive domains such as memory, executive function, attention, language, abstraction, naming, delayed recalls, and orientation.^[30]^ In order to avoid false increase of participants’ cognitive-function test results caused by repeated tests, we will use different versions of MoCA, including 7.1, 7.2, 7.3, and basic of MoCA.

We also choose Clinical Dementia Rating Scale (CDR) to evaluate cognitive function. A CDR of 0.5 is established risk states for dementia.^[31]^ Compared with MMSE, although CDR score is not predictive of change in cognitive performance, it is predictive of functional change over time and of conversion to dementia.^[32]^

### Incidence of PSD

3.8

We will use MMSE, which is the most widely used by frontline physicians, to detecting dementia. Dementia: MMSE score ≤17 (illiteracy), or MMSE score ≤20 (primary school culture), or MMSE score ≤24 (middle school and above).^[33]^

## Secondary outcome

4

### Instrumental activities of daily living (IADL)

4.1

Compared with basic ADLs, functional changes are noted earlier in the dementia process with instrumental activities of daily living (IADLs).^[34]^ We will use the Functional Activities Questionnaire (FAQ), which has a wide application to measure the IADLs. The target population of FAQ includes adults with normal cognition, MCI, as well as mild, moderate, and advanced dementia.^[35]^

### Neuropsychiatric inventory (NPI)

4.2

The evaluation of neuropsychiatric symptoms is an important part of dementia diagnosis and management.^[36]^ The 12-item version of neuropsychiatric inventory (NPI) will be used in this trial. Compared with the original NPI with 10 items, this version added the elements of sleep/nighttime, behavior disturbances, and appetite/eating disturbances.^[37]^

### Quality of life (QOL)

4.3

The cognitive decline has a great influence on the quality of patience's life. In this trail, QOL will be evaluated by WHOQOL-BREF Chinese Scale.

### Amyloid-β

4.4

Previous studies^[38]^ showed that stroke can enhance the vascular deposition of amyloid-β (Aβ), which induced cognitive decline and post-stroke cognitive impairment. For the 2 main forms of Aβ, the 40-amino acid form (Aβ 40) and the minor 42-amino acid form (Aβ 42), the aggregates of Aβ42 is neurotoxic and is more readily than Aβ 40.^[39]^ So, this trial choose Aβ 42 as the laboratory index.

The patients’ blood samples will be collected and analyzed twice, one before the treatment, another after 3 months treatment. The blood sample (5 mL) from each patient will be taken under aseptic conditions from the antecubital vein and will be placed in EDTA anticoagulant tubes. After centrifugation at 3000 r/min for 10 minutes, the extracted serum will be put into tubes and be stored at −80°C until the analysis. The level of plasma Aβ42 will be detected by the enzyme-linked immunosorbent assay (ELISA).

## Data management and quality control

5

The third party is fully responsible for the data management of the project. Specific research assistants (RA), who are masked to treatment allocation, will double-enter the data electronically. Data will be collected by medical records, asking patients, participants’ relatives, caregivers, or proxies directly. The personal information of the participants will be kept in specific files with pre-set codes. Entering data into eCRFs and other essential skills were covered during the training session before study commencement.

We will set up a quality control group to guarantee the validity and reliability of results. Every 3 months, members of the quality control group will perform a quality control review at each hospital and produce a report regarding the quality analysis of the research process.

## Safety evaluation

6

Subcutaneous hemorrhage, hematoma, syncope, stuck-needle are the common adverse events (AE) of acupuncture treatment. We will record all the adverse events of acupuncture during the intervention and follow-up period. The proportion, type, and potential reasons of AEs will be calculated. All AEs will get appropriate intervention and serious AEs will be reported to the ethics committee immediately.

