### Blinding

2.8

Assessors who are masked to treatment allocation and trained will be in charge of baseline evaluation and measurement. Patients who receive acupuncture treatment will not be aware of their group assignment. However, the waiting-list group cannot be blinded. Because different acupuncture treatments are used in AG and NAG, it is impossible to blind the acupuncturists. During the trial period and follow-up phases, the third party and assessors will all be blinded.

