### Follow-up

3.4

After the 12-week intervention period, all participants will enter an additional 24-week follow-up period. Participants will be followed up per 12 weeks since the treatment end. Assessors will contact with the participants by telephone before the follow-up date. If there is no response to the telephone contact for 1 consecutive week, or the patient expresses that he/she does not want to cooperate with the follow-up, he/she will be listed as lost, the follow-up work should be stopped.

Participants will be given acupuncture treatment when the follow-up period is completed, in order to reduce the shedding rate.

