### Outcome assessment

3.5

In this trail, most primary and secondary outcomes will be measured at baseline, the end of intervention(12weeks), after an additional 12-week follow-up period (24 weeks) and after an additional 24-week follow-up period (36 weeks). Amyloid-β and fMRI will be measured at baseline and the end of intervention. A summary of all the measures in the trial is summarized in Table 3.

**Table 3 T3:** Outcome measurements at each timepoint.

Study period	Enrolment	Intervention	Follow-up	
STUDY TIMES	The first time	The second time	The third time	The fourth time
TIME POINT	−3d-0	12 wks ± 3d	24 wks ± 3 d	36 wks ± 3d
MoCA	×	×	×	×
MMSE	×	×	×	×
CDR	×	×	×	×
NPI	×	×	×	×
WHOQOL-BREF	×	×	×	×
FAQ	×	×	×	×
β-Amyloid	×	×		
Adverse Reaction/Event		×	×	×
Vital signs	×	×	×	×
Recurrence		×	×	×
Using drugs	×	×	×	×
Laboratory examination	×	×		

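### The safety section ties adverse-event recording to acupuncture, which is narrower than Table 3 and may leave the waiting-list arm without a comparable event rate

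*Protocol article*

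**What the plan says.** Section 6 (Safety evaluation) opens with examples that all belong to needling: "Subcutaneous hemorrhage, hematoma, syncope, stuck-needle are the common adverse events (AE) of acupuncture treatment". The recording rule follows: "We will record all the adverse events of acupuncture during the intervention and follow-up period". The summary is then described as "The proportion, type, and potential reasons of AEs will be calculated", and handling as "All AEs will get appropriate intervention and serious AEs will be reported to the ethics committee immediately". These last two sentences drop the link to acupuncture.

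Other parts of the article are wider:

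- Section 3.5 says "A summary of all the measures in the trial is summarized in Table 3". That table has a row "Adverse Reaction/Event" marked at 12, 24 and 36 weeks, and a separate row for recurrence at the same visits. Neither is limited by arm or cause.
- Section 2.6 ends participation for any participant who has a serious adverse event, whatever the arm.
- Section 3.4 says "all participants will enter an additional 24-week follow-up period".
- Section 3.3 gives the waiting-list group standard treatment only for the first 36 weeks. Section 3.2 has the sham group needled too, shallowly and at non-acupoints.

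**The concern.** The article gives two different scopes for the same data. A site working from Section 6 would ask whether an event came from acupuncture and record it if so. A site working from Table 3 would record any adverse event in any participant. With five hospitals, both practices could occur in one trial.

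The waiting-list group is where this matters most. It is the only arm without needles, so it alone shows the background event rate under standard treatment, and it alone can reveal harm shared by real and sham needling. If an event must first be attributed to acupuncture, that arm has nothing to contribute. An event in a needled arm that nobody connects with needling would also be lost. Participants are within six months of an ischaemic stroke, so medical events unrelated to needles are plausible in every arm. A randomised comparison separates an excess from that background without relying on anyone's causal judgement.

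**Working it through.** The protocol states no adverse-event rate, safety sample size or safety power, so there is no figure to reproduce. The check is a comparison of passages, followed by an illustration with assumed rates.

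**Passages side by side**

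| Place | Scope by cause | Scope by arm |
|---|---|---|
| Section 6, recording sentence | events of acupuncture | not stated; a waiting-list patient cannot have one in the first 36 weeks |
| Section 6, last two sentences | no qualifier | not stated |
| Table 3, adverse-event row | none | none |
| Table 3, recurrence row | stroke recurrence | none |
| Section 2.6, withdrawal | serious adverse events, any cause | all participants |

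The recording sentence is the narrowest entry. The last two sentences of Section 6 do not clearly widen it, because the abbreviation AE is introduced there as part of a phrase about acupuncture treatment.

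**Timing.** Trial needling stops at 12 weeks and is not offered again until follow-up is complete at 36 weeks. Section 6 nevertheless records through follow-up, and Table 3 collects at 24 and 36 weeks. New needling events of the kind listed could hardly arise in that window, so the schedule fits any-cause recording better than the literal wording does.

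**Illustration.** Arm size is 360/3 = 120. Assume any-cause event rates of 5% in the waiting list (6 of 120) and 10% in the acupuncture group (12 of 120).

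- Any-cause recording: difference = 10% − 5% = 5 points. Standard error = √(0.10×0.90/120 + 0.05×0.95/120) = √(0.000750 + 0.000396) = 0.0339. The 95% interval is 5 ± 1.96×3.39, or about −1.6 to 11.6 points.
- Literal Section 6: the waiting list records 0. If a share a of acupuncture-group events is attributed to needling, the recorded difference is a×10% − 0. As a runs from 0 to 1 this goes from 0 to 10 points. The result depends on a, and the 5-point excess is not what is being estimated.
- Harm common to both needled arms: let the sham rate also be 10%. Real minus sham = 0; real minus waiting list = 5 points. Only the second contrast shows the harm, and it needs the waiting-list events.

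**What full recording would buy.** Power for two arms of 120, two-sided 0.05, with p̄ the mean of the two rates:

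Φ{[|p₁ − p₂| − 1.96√(2p̄(1 − p̄)/120)] / √[p₁(1 − p₁)/120 + p₂(1 − p₂)/120]}

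For 5% versus 10%: (0.05 − 1.96×0.0340)/0.0339 = −0.49, so power is about 31%. The same formula gives about 74% for 5% versus 15%, 75% for 2% versus 10% and 87% for 1% versus 10%. All these rates are assumptions. Full recording gives an unbiased comparison, but as a formal test it detects only fairly large excesses.

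**The case against.** The best defence is that this is one loose phrase in a condensed article. Table 3 covers all measures and exempts no arm, everyone is followed up, the withdrawal rule presupposes that serious events are known in all arms, and recurrence is collected separately. The needling events in Section 6 are given as common examples and do not amount to a definition. Calculating potential reasons for events fits recording first and asking about cause afterwards. Detailed adverse-event procedures may also sit in a full protocol that is not shown.

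Much of this stands, and it rules out several stronger readings that a reader might infer:

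- That the waiting-list arm will have no event rate. No passage excludes it, and Table 3 points to collection there.
- That the trial cannot show whether acupuncture causes excess harm. Real and sham groups share a treatment schedule and can be compared even on the literal wording; what that comparison misses is harm common to both.
- That unblinded acupuncturists decide what is recorded. Section 2.8 says "it is impossible to blind the acupuncturists", but no passage makes them the recorders or judges of adverse events. The same section puts masked assessors in charge of measurement, and Section 5 draws data from records, patients and caregivers, with masked entry.
- That more frequent contact in the needled arms is itself an error. It comes with a no-treatment control, and every arm has the same scheduled adverse-event visits in Table 3.

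The defence does not remove the conflict. The point does not rest on missing detail: Section 6 states a recording rule, and that rule is narrower than the article's own schedule.

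**Conclusion.** The concern holds as a contradiction in recording scope, with a conditional consequence. If Section 6 is followed as written, recording depends on attribution to needling, the waiting-list arm may lack a comparable event rate, and harm shared by real and sham needling could not be seen. If Table 3 is followed, the data will be there. The article does not say which governs.

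Its size cannot be derived from the protocol. The 5% and 10% rates are assumed, and the zero in the waiting list holds only on the literal reading. They show that the any-cause excess would not be estimable under that reading; they are no forecast of event rates. The correction is worth making because it is cheap and replaces a stated rule that would bias the safety comparison if followed.

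**What to change.** Reword Section 6 to match Table 3: all adverse events, whatever their cause, are recorded in all three arms at the existing 12-, 24- and 36-week visits. Relatedness to acupuncture goes in a separate field, completed after the event is recorded. Any-cause and serious events are summarised by arm from those visits. Needling events seen at treatment sessions are reported separately for the acupuncture and sham groups, since the waiting list has no sessions.

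The cost is a short rewording, one extra case report form field and a few more recorded events. No new visit is needed, and no treatment or clinical rule changes.

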## fMRI acquisition

7

### Objective

7.1

In terms of brain network and brain functional connections, this trial also aims to explore the mechanism of acupuncture treatment for cognitive impairment after stroke.

### Participants

7.2

Twenty eligible participants will be screened in each group (AG, NAG, WLG).

### Method

7.3

Resting-State fMRI Acquisition.

### Assessment

7.4

For AG and NAG, fMRI data will be collected at enrollment and after the last treatment. For WLG, fMRI data will be collected once at enrollment and after 3 months.

### Sample size and statistical methods

7.5

The sample size calculation is based on the improvement of Montreal cognitive assessment scale (MoCA) scores, which has a higher sensitivity than MMSE for MCI.^[7]^ According to the similar published articles,^[40]^ the mean difference in MoCA scores between AG and control group (CG) is 1.5, with a standard deviation of 1.13 in AG and 1.20 in CG. According to our previous study, acupuncture treatment can probably improve the MoCA by 0.6 on average compared with control group. Considering a 1-sided significance level of 0.025 and power of 95%, 95 participants are required for each group, as calculated by PASS 11 software. To minimize attrition bias, we assumed the dropout rate of 20%, making it necessary to include at least 357 participants with a 1:1:1 group allocation rate. We plan to enroll 360 participants in total.

Continuous variables are presented as mean (SD) if they obey normal distribution, and paired-sample *t* test will be used in intragroup comparison; if they are not normal distribution, median (quartile interval) [M(IQR)] will present them, and Wilcoxon rank sum test will be used in intra-group comparison; Variance analysis will be used for comparison between groups which is consistent with the normal distribution and homogeneity of variance; if not, then Mann–Whitney *U* test will be used. Group comparisons will then be undertaken using χ^2^ tests for categorical characteristics. Two-sided *P* < .05 represents statistical significance for all the analyses.

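### The stated 95 per group is 4 to 5 short of what the printed inputs give for 95% power; at those inputs the design has about 94% power (minor)

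*Protocol article*

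**What the plan says.** All of this stands in section 7.5 of the protocol article. The endpoint used for sizing is change in MoCA: "The sample size calculation is based on the improvement of Montreal cognitive assessment scale (MoCA) scores". Two differences follow. From published work, "the mean difference in MoCA scores between AG and control group (CG) is 1.5". The same source supplies the spread in each arm, given as "with a standard deviation of 1.13 in AG and 1.20 in CG". From the sponsor's own earlier study, "acupuncture treatment can probably improve the MoCA by 0.6 on average compared with control group". The error rates come next: "Considering a 1-sided significance level of 0.025 and power of 95" (per cent). The result is that "95 participants are required for each group, as calculated by PASS 11 software". For attrition, "we assumed the dropout rate of 20" (per cent). The inflated total is then stated as "making it necessary to include at least 357 participants with a 1:1:1 group allocation rate", and planned enrolment is 360. The same section later sets two-sided P < .05 for every analysis. It mentions no adjustment of the significance level for multiple comparisons. The trial has three arms (acupuncture, sham acupuncture, waiting list), and the sizing text does not say which of the two controls is meant.

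**The concern.** A reader should be able to enter the printed difference, standard deviations, significance level and power and get the printed sample size. Here that fails. The section gives two differences without saying which was entered, and neither yields 95 with the other printed inputs. What is at stake is the accuracy of the stated power and the reader's ability to tell which difference, against which control, the trial was designed to detect.

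**Working it through.** **Inputs (all from section 7.5).** Difference 0.6 (own earlier study) or 1.5 (published work); SD 1.13 and 1.20; one-sided level 0.025; power 95%; dropout 20%; 95 per group; at least 357 in total; 360 planned.

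**Attempt to reproduce 95.** For two means with equal group sizes, the normal approximation is

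n = (z₁₋α + z₁₋β)² × (SD₁² + SD₂²) / δ²

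- (1.960 + 1.645)² = 12.995 (from unrounded z values)
- 1.13² + 1.20² = 1.2769 + 1.4400 = 2.7169
- δ = 0.6: 12.995 × 2.7169 / 0.36 = 98.07, so 99 per group. The noncentral t calculation gives 100.
- δ = 1.5: 12.995 × 2.7169 / 2.25 = 15.69, so 16 per group. The t calculation gives 17.

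The 95 is not reproduced. The nearer reading, 0.6, misses by 4 to 5 per group.

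**Dropout step.** 95 / 0.8 = 118.75, so 119 per group, and 3 × 119 = 357. This agrees with the article, so the discrepancy lies in the 95 and its inputs. For comparison, 99 / 0.8 = 123.75, so 124 × 3 = 372, and 100 / 0.8 = 125, so 125 × 3 = 375.

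**Power at the stated size (δ = 0.6, both SDs, one-sided 0.025).**

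- 95 per group, normal: 0.6 / √(2.7169 / 95) = 3.548; 3.548 − 1.960 = 1.588; power 94.4%.
- 95 per group, t test: 94.2%, and the same with unequal variances (Welch).
- 360 enrolled: 120 × 0.8 = 96 per group; t test 94.4%.

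**Settings that come to 95 or close to it (δ = 0.6 unless stated).**

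| Change from the printed inputs | n per group |
|---|---|
| δ = 0.61, all else as printed | 12.995 × 2.7169 / 0.3721 = 94.9, so 95 (normal) |
| δ = 0.615, all else as printed | 95 (t) |
| SD 1.13 in both arms, all else as printed | 93 (normal), 94 (t) |
| One-sided 0.0125 and 90% power, both SDs | 94 (normal), 95 (t) |
| SD 1.20 in both arms, one-sided 0.05/3 and 90% power | 94 (normal), 95 (t) |

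Several different routes therefore lead to about 95. The first two keep the printed level, power and SDs, and need only a difference that prints as 0.6 to one decimal place.

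**The case against.** The strongest defence is that nothing of substance is wrong. The 0.6 is given to one decimal, so an unrounded software input of about 0.61 to 0.615 would explain 95 without touching the significance level or the power. Taking SDs from the literature and a more cautious difference from one's own data is ordinary practice. A size of 95 cannot come from 1.5, so 0.6 was evidently the design difference. And 94% power is close to the 95% claimed. Most of this stands: it fixes the size of the point as small, and it means that 1.5 is not a live alternative. It does not make the printed figures agree, and the unrounded input is a possibility that the article does not confirm.

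A reader might go further and infer that the significance level was split over two comparisons, because one-sided 0.0125 with 90% power also gives 95 by the t test, and that the later rule of two-sided .05 throughout therefore contradicts the sizing. The article does not support this. That route replaces both the printed level and the printed power, it is only one of several that reach 95, and no split is mentioned. As printed, one-sided 0.025 corresponds to two-sided .05, so the two statements agree.

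**Conclusion.** The sample size and power in section 7.5 do not match the printed inputs: 99 to 100 per group would be needed where 95 is stated. The effect is small. Power is about 94.2% at 95 per group and 94.4% at the 96 expected to remain, a shortfall of 0.6 to 0.8 percentage points. This rests on a two-group comparison of means with δ = 0.6, SDs of 1.13 and 1.20, one-sided 0.025, and 20% loss in each arm. The source of the discrepancy cannot be identified from the article. It is a minor reporting error and does not show that the trial is materially underpowered for 0.6. Leaving the comparator unnamed does not change the arithmetic, but it does leave open which contrast the stated power refers to.

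**What to change.** Keep enrolment at 360 and correct the text of section 7.5 in one of two ways.

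1. Restate the figure: *96 evaluable participants per group give about 94% power for a 0.6-point difference in MoCA (SD 1.13 and 1.20) at one-sided 0.025 (two-sided 0.05).*
2. Or check the saved software output and print the exact difference and SD that were entered, so that 95 can be reproduced.

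In either case, say that 0.6 is the design difference and that 1.5 is background, and name the control (sham or waiting list) used in the powered comparison. The cost is a few sentences. Under the first option the stated power drops by about one point; the sample size, conduct and analysis do not change.

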## Ethics approval and consent to participate

9

The ethic committee of First Teaching Hospital of University of Traditional Chinese Medicine approved the study. We have also registered at ClinicalTrials.gov (http://www.chictr.org.cn/showprojen.aspx?proj=54764): ChiCTR2000033801. All patients gave their written informed consent before participating in the clinical trial. The details of our study, including trial objectives, characteristics, probable benefits and risks, other available treatment alternatives, and the subjects’ rights as well as obligations as stated in the Declaration of Helsinki, will be made clear to the patients by a study personnel who has their grouping code, and their agreement will be required. After obtaining the written informed consent, the subjects will be enrolled in the study. During the process of the trial, if new points regarding the study ethics emerge, written revisions regarding the informed consent will be handled by the Ethics Committee and, after their approval, the individuals’ consent will be requested again. In case of the patients’ withdrawal, their available data will be kept for the final analyses.

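### The 20% dropout allowance is presented as minimising attrition bias but only preserves power, and the tests named use withdrawn patients' scores incompletely

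*Protocol article*

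**What the plan says.** Section 7.5 of the protocol article introduces the dropout allowance with its purpose: "To minimize attrition bias, we assumed the dropout rate of 20" per cent, "making it necessary to include at least 357 participants with a 1:1:1 group allocation rate". It then names the analyses. Within groups, "paired-sample *t* test will be used in intragroup comparison", with a Wilcoxon test if the data are not normal. Between groups, it names analysis of variance, or Mann-Whitney if the assumptions fail, and chi-square tests for categorical data.

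Section 9 adds: "In case of the patients’ withdrawal, their available data will be kept for the final analyses".

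Three other places bear on who is likely to be missing. Section 2.6 ends participation on deterioration or a serious adverse event. Section 3.4 stops follow-up once a patient is listed as lost. Section 2.8 notes: "However, the waiting-list group cannot be blinded", and section 3.3 leaves that group on standard treatment alone for 36 weeks. Section 3.5 schedules the scales at baseline and at weeks 12, 24 and 36.

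**The concern.** Recruiting more patients replaces lost information. It does not change which patients are lost. If those who leave would have scored differently from those who stay, and this differs by arm in frequency or in degree, the comparison of remaining patients is off by the same amount in a large trial as in a small one. The stated reason for the 20% is therefore wrong, and a reader may believe that attrition bias has been dealt with.

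The plan itself makes such loss plausible. The primary outcome is cognitive function and incidence of post-stroke dementia, and deterioration is a ground for ending participation. One arm knows that it is waiting while the other two receive needling three times a week, so equal dropout cannot be taken for granted.

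The named tests matter because they determine how much a leaver's recorded scores can help. At weeks 24 and 36, where the article claims long-term evidence, they help little.

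**Working it through.** **Inputs from section 7.5.** Effect: "acupuncture treatment can probably improve the MoCA by 0.6 on average compared with control group". Spread: "with a standard deviation of 1.13 in AG and 1.20 in CG". Design: "Considering a 1-sided significance level of 0.025 and power of 95%, 95 participants are required for each group". Dropout 20%; 357 required, 360 planned. **Not in the document, so assumed below:** dropout by arm, and the difference between leavers and stayers.

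**1. Base number.** n = 2 × SD² × (1.960 + 1.645)² / 0.6². With SD 1.13 this gives 93 per group (94 by t test). With the pooled SD, √((1.13² + 1.20²)/2) = 1.17, it gives 99 (100 by t test). The stated 95 lies between these; with the pooled SD its power is 94.4%. This small gap is a separate matter.

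**2. The inflation reproduces exactly.** 95/0.8 = 118.75, rounded up to 119; 3 × 119 = 357. Against 3 × 95 = 285, that is 357/285 = 1.253, or 25% more. At 20% loss, 360 × 0.8 / 3 = 96 evaluable patients per group. The allowance does what a power allowance should.

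**3. What it does to precision.** Standard error of the completers' difference = SD × √(2/m), with m = 0.8N. For N = 95, m = 76 and the standard error is 0.189. For N = 119, m = 95.2 and it is 0.169.

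**4. What it does to bias.** In an arm with dropout share p, and stayers scoring g points above what leavers would have scored, the completers' mean exceeds the full mean by p × g. The bias in acupuncture minus waiting list is p(AG) × g(AG) − p(WLG) × g(WLG). N does not appear.

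**5. Illustrations, all on assumed values.**
- Same gap in both arms, 0.6 to 1.17 points (about 0.5 to 1 SD), dropout 15% against 25%: 0.10 × 0.6 = 0.06 and 0.10 × 1.17 = 0.117, which is 10 to 20% of the planned 0.6.
- Same gaps, dropout 10% against 30%: 0.20 × 0.6 = 0.12 and 0.20 × 1.17 = 0.234, which is 20 to 39% of 0.6.
- Dropout 20% in both arms, gap larger in the acupuncture group by 0.5, 1 or 2 points: 0.2 × 0.5 = 0.10, 0.2 × 1 = 0.20 and 0.2 × 2 = 0.40.
- Dropout and gap both equal across arms: zero.

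The first two give magnitudes. The direction depends on whether leavers are worse or better than stayers.

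**6. Check by simulation.** There was no true effect and about 20% dropout in each arm, random in control and more likely for low scorers in the acupuncture group. The mean bias was 0.168, 0.170, 0.170 and 0.170 at 95, 119, 120 and 1000 per arm.

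**7. Consequence for error rates.** With the bias fixed at 0.20 (the case of a gap larger by 1 point), the nominal one-sided 2.5% error rate is 18.3% with 95 enrolled per arm and 21.9% with 119. More patients make a biased comparison more confident.

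**8. How far the named tests use leavers' scores.** A paired test needs baseline and the visit in question; a between-group test needs a value at that visit.
- Leaves before week 12: contributes to no post-baseline test.
- Leaves between weeks 12 and 24: contributes at week 12, but not at weeks 24 and 36.
- Leaves between weeks 24 and 36: contributes at weeks 12 and 24, but not at week 36.

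If analysis of variance instead means the classical repeated-measures form, a patient with any missing visit is normally deleted altogether, which uses still less.

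**The case against.** A reader might infer that the named tests cannot use withdrawn patients' data at all, and so contradict section 9. The document does not support that. Earlier scores enter the earlier comparisons, and section 9 promises only to keep what is available, not to make each patient count at every visit. That promise is partly served, not broken.

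The visit-by-visit reading is itself inferred from the tests and the schedule; section 7.5 does not use the term. Imputation, analysis sets and missing-data methods are commonly left to an analysis plan, which is not shown, so their absence is not a fault here, and the named tests could be run on imputed data. The plan also has a retention measure: section 3.4 offers acupuncture after follow-up in order to limit dropout, which could help to keep the waiting list.

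A reader might also take the bias figures as a forecast. They are not. The plan gives one overall rate of 20%; applied equally, with equal gaps, it yields no bias. The smallest figure, 0.06, is about a third of the standard error of 0.169.

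Finally, deleting the phrase on attrition bias would by itself change no result, and a mixed model gains nothing from a patient with baseline data alone.

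All of this stands. It limits the size of the point but does not rescue the stated rationale, and it does not alter the fact that section 7.5 commits to tests for which a better standard alternative exists.

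**Conclusion.** The point holds in a limited form. The stated purpose of the 20% allowance is wrong: going from 285 to 357 preserves power and leaves bias from informative dropout unchanged at any sample size. The rules in sections 2.6 and 3.4 make such dropout plausible but do not prove it. The tests fixed in section 7.5 use withdrawn patients' scores incompletely, most clearly for the between-arm comparisons at weeks 24 and 36; this rests on reading them per visit, and the repeated-measures reading is no better.

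The size is unknown. The 0.06 to 0.23 MoCA points depend wholly on the assumed dropout splits and leaver-stayer gap, and could be zero or of either sign. The sample size is not in question on this ground. This is a worthwhile, cheap improvement rather than a flaw that endangers the trial.

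**What to change.** In section 7.5, drop the claim about attrition bias and say that the 20% allowance preserves the number of evaluable patients.

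For the continuous scales, make the main between-arm analysis a mixed model for repeated measures with arm, visit, arm by visit and baseline score, using every observed week 12, 24 and 36 score. A patient whose decline is recorded at week 12 and who then leaves will inform the later estimates through that score.

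Add one delta-adjusted sensitivity analysis: impute the missing scores, including those of patients who left before week 12, shift them by a prespecified amount that may differ by arm, and report how far the arm difference moves.

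The cost is protocol or analysis-plan wording and modest extra programming, with no extra patients or visits. The downside is that the model assumes data missing at random, which the sensitivity analysis probes but cannot verify. The change does not address incidence of post-stroke dementia, which needs its own statement on patients who leave.
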